#### Sample size and power calculation

The required sample size was calculated based on the primary outcome measure of self-reported pain [109]. A meta-analysis defined a clinically significant reduction in pain as a change of Δ = − 2 (on a scale of 0–10) [110]. The sample size required to detect a pain reduction of this magnitude between RS2 and RS3 was estimated. The risk of type I error was set at 5% and the risk of type II error was set at 10%, giving 90% power to detect a significant change in the pain. The standard deviation expected in the current study was estimated as 1.98 based on pain intensity ratings obtained by our group in recent research [8]. Given these parameters, a minimum of 42 participants with CRPS (21 per group) is required to evaluate the effects of the PA treatment on the primary outcome measure of pain. Taking into account an anticipated drop-out rate of 20%, up to 52 participants with CRPS will be enrolled in order to obtain a total of at least 21 complete datasets for RS1-RS4 per treatment group. To provide normative data, 21 healthy (pain-free) control participants will be recruited.

#### Timing

No interim analyses are planned. The timing of the final analyses will be stratified by planned length of follow-up for the relevant outcome measures. Once all participants have completed RS4, we will analyse the RS1-RS4 data to address our research questions regarding the efficacy of PA treatment in reducing CRPS symptom severity (RQ1) and the relationships between the severity of clinical symptoms of CRPS and neuropsychological changes in perception of and attention to the affected limb and its corresponding side of space in RS1 (RQ5). We will conduct separate analyses of current self-reported pain intensity, the BPI, the Pain Detect Questionnaire, the BPDS, the Tampa Scale for Kinesiophobia, the Profile of Mood States, and the Patient’s Global Impression of Change scores once all participants meet the secondary endpoint (LTFU2). Recruitment will be terminated if we are not able to collect 42 full datasets for RS1-RS4 by 1 March 2019.

#### Treatment outcome analyses

We will conduct intention to treat (ITT) as our primary analysis to examine the overall effects of prism adaptation. The ITT analysis will include all allocated participants with CRPS regardless of treatment adherence and completion of outcome measurements. Baseline post-randomisation observation (RS2) carried forward will be used to account for missing data in ITT analysis, as the participants are expected to return to pre-treatment baseline over time. The exception is the Patient Global Impression of Change questionnaire that is only completed in the post-treatment research sessions, in which case the RS3 observation will be carried forward. Missing data from the computer-based tasks within each research session will be replaced by group mean for the particular task condition (with an exception of Directional Hypokinesia task, where some participant with CRPS may not be able to complete the task using the affected limb; in such cases only the conditions completed with the unaffected limb will be analysed). Missing daily logbook ratings will be interpolated using linear regression.

We will also conduct a supportive per-protocol (PP) analysis to see whether PA treatment can benefit the participants with CRPS who were able to perform it according to the trained protocol compared to those participants who were able to complete the sham treatment according to trained protocol [111]. The PP population will be the subset of the ITT population who provided complete outcome data for RS1-RS4 (i.e. attended all in-person research sessions and completed the primary outcome measures) and missed no more than 6 treatment sessions.

We will use confidence intervals to compare the RS1 primary outcomes scores of the participants with CRPS who withdrew and those who remained in the trial until RS4 to assess any potential selection bias. The timing and reasons for withdrawal will be presented in a CONSORT diagram.

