### Participants

#### Eligibility criteria

##### Participants with CRPS

This study enrols both male and female individuals, who:
are willing and able to give informed consent to take part in the trial,are aged 18–80,have a diagnosis of CRPS type I based on the Budapest diagnostic research criteria [2] as assessed at RS1 and revisited at RS2,have CRPS type I primarily affecting one upper limb,have had CRPS for a minimum of 3 months at the time of RS1,and report current pain intensity ≥2 on a 0–10 Numeric Rating Scale at RS1 and RS2.

Participants are excluded from the CRPS group if they:
lack sufficient English language ability to provide informed consent,are classified as legally blind,have a history of neurological disorder (e.g. stroke, neurodegenerative disease or traumatic brain injury),have CRPS meeting the Budapest diagnostic clinical or research criteria affecting both sides of the body,^2^report that they have confirmed presence of nerve damage (CRPS type II) based on the results of nerve conduction test,have dystonia or any other physical limitation severe enough to prevent satisfactory execution of PA/sham treatment,or have a severe psychiatric comorbidity (such as schizophrenia) that in the researchers’ opinions would compromise participation in the study.

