#### Effects of PA treatment on neuropsychological changes and other secondary outcomes (RQ2) and time course of any improvements (RQ3)

To analyze between-group (PA treatment vs. sham treatment) differences on the secondary outcome measures (see Table 3) across four (RS1-RS4) or six (RS1-LTFU2) time points, we will conduct 2 × 4 or 2 × 6 ANOVAs as described for the analyses of the primary outcomes. Specifically, a 2 × 4 ANOVA will be run on each clinical assessment outcome (limb temperature asymmetry, hands size difference, grip strength and ΔFTP ratios, MDT, MPT, two-point discrimination threshold ratios, and allodynia) and mean group scores in the following computer-based measures: PSSs in the TOJ task, PSEs in the Landmark task, attention bias scores in the Greyscales task, and bias scores in the MNLB task. We will also use 2 × 4 ANOVAS to analyse between-group differences on indices A and B for the affected and unaffected hand performance in the Directional Hypokinesia task, as well as on hand laterality recognition accuracy and RTs indices in the Hand Laterality Recognition task across RS1-RS4. Separate 2 × 6 ANOVAs will be run on mean group scores on each of the self-reported questionnaire measures: pain intensity and interference components of the BPI, the Pain Detect Questionnaire, The BPDS, the Tampa Scale for Kinesiophobia, and the Profile of Mood States.

We will plot group means of daily ratings of average pain, range of movement, and interference over time and use contrasts to identify the time points of significant group differences. We will also identify for both groups and for each measure the average number of days to reach peak improvement from the start of treatment, and the average number of days from the peak improvement to return to baseline.

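### The affected-hand Directional Hypokinesia comparison of PA with sham is a subset analysis that may depend on post-allocation ability, not ITT as the protocol defines it

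*Protocol article*

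**What the plan says.** All of the missing-data rules are in the protocol article under Treatment outcome analyses. The analysis set is defined first: "The ITT analysis will include all allocated participants with CRPS regardless of treatment adherence and completion of outcome measurements". The general filling rule follows: "Baseline post-randomisation observation (RS2) carried forward will be used to account for missing data in ITT analysis". Computer-based tasks have their own rule: "Missing data from the computer-based tasks within each research session will be replaced by group mean for the particular task condition". The Directional Hypokinesia task is exempted from that last rule because "some participant with CRPS may not be able to complete the task using the affected limb", and "in such cases only the conditions completed with the unaffected limb will be analysed".

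The section on RQ2 and RQ3 then plans 2 × 4 ANOVAs (arm by RS1–RS4) of "between-group differences on indices A and B for the affected and unaffected hand performance in the Directional Hypokinesia task". The opening of Statistical analyses keeps ANOVA as the default and turns to linear mixed models only when assumptions are severely violated. Under Design, allocation falls 1–5 days before RS2, and treatment starts after RS2.

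**The concern.** The exemption is attached to data missing in any research session and sets no time limit. It therefore covers a participant who could do the task before treatment and cannot do it at RS3 or RS4. Use of the affected limb is part of the condition under treatment; motor abnormalities count towards the CRPS severity score. Whether someone stays in the affected-hand comparison may thus depend on a state that allocation can change.

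Two things are at stake for these indices. One is comparability of the arms, if the numbers becoming unable differ between them. The other is precision, because a single missed session can cost a participant's other three in a trial planned around 21 per group.

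**Working it through.** The plan gives no figure for how many participants will be unable, so there is none to reproduce. The check sets the rules side by side and then shows what assumed rates would imply.

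**Step 1: two participants under the stated rules.** Participant X withdraws before RS3. RS2 is carried forward and X stays in the ITT analysis. Participant Y attends RS3 but cannot do the task with the affected limb. Y's affected-limb conditions are left unanalysed. A repeated-measures ANOVA in its usual form has no place for a participant with three of four sessions, so Y leaves the affected-hand comparison altogether. Complete-case handling is a property of the default method; the protocol does not state it in words.

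**Step 2: participants lost.** Let p be the assumed proportion unable at each session. If the same people are unable every time, the loss is p. If inability is independent across sessions, the loss is 1 − (1 − p)^4.
- p = 5%: from 5% to 1 − 0.95^4 = 18.5%. Of 42 participants that is about 2 to 8.
- p = 10%: from 10% to 1 − 0.90^4 = 34.4%, about 4 to 14 of 42.

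**Step 3: when the comparison is biased at RS3.** A simulation took a true PA effect of −0.50 SD on an affected-hand index, with people unable once a symptom score passes a threshold. The assumed ranges were 10–30% of sham unable and an index–symptom correlation of 0.3–0.6.
- PA lowers symptoms by 0.5–1.0 SD: about 1–15% of PA are unable, and the difference among those able is −0.47 to −0.28 SD. The bias is 0.03 to 0.22 SD toward no effect.
- PA has no effect on symptoms: bias 0.
- Inability set by a pre-allocation state (20% unable, correlation 0.6, symptom effect 1.0 SD): bias 0.

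**Step 4: change from RS2 to RS3.** The protocol says it is primarily interested in this change for the primary outcomes, and it analyses the secondary outcomes in the same way. Removing k of n participants who average 1 SD worse moves the remaining mean by −k/(n − k). Take 26 per arm (half of the maximum enrolment of 52), with 5 sham and 1 PA participants unable, all assumed. Sham moves by −5/21 = −0.238 SD and PA by −1/25 = −0.040 SD, a gap of 0.198 SD in the RS3 means. Deleting these people also deletes their RS2 values. If they were r SD worse at RS2, the bias in change is 0.198 × (1 − r): 0.099 SD at r = 0.5, and 0 at r = 1.

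**The case against.** The strongest reply is that the exemption is disclosed and sensible. No reaction time exists for a movement that cannot be made, and filling it with a group mean would be poor practice. That stands: the weakness is the rule's reach and the ANOVA behind it, not the refusal to impute.

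It can also be said that removal from the whole comparison is inferred. The exemption qualifies group-mean filling within a session and is not worded as an exception to carrying RS2 forward. A reading in which only the missed session is lost is open. That is fair, but the sentence takes the affected-limb conditions out of the analysis, and the default ANOVA cannot use the sessions that remain.

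A reader might infer that inability must be a worsening after allocation, because the protocol already excludes people who "have dystonia or any other physical limitation severe enough to prevent satisfactory execution of PA/sham treatment". The documents do not support this. That criterion concerns a pointing exercise of about 5 minutes. The task requires holding down a button with the index finger, start positions 25 cm to either side, and three 30-trial blocks with the affected hand, within a session of 2–4 hours. Someone may manage the treatment and be unable to do the task from RS1 onward.

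A reader might also infer that the worst performers vanish and that PA is disadvantaged by about 0.2 SD. That is not supported either. Indices A and B are differences between times of the same hand, so general slowness largely cancels. The 1 SD deficit and the 5-to-1 split are assumptions, and the shift shrinks when change is analysed. Finally, the protocol defines directional hypokinesia as present whichever arm is used, and the unaffected-hand indices are analysed separately.

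**Conclusion.** The point holds in a limited form. As written, the affected-hand PA–sham comparison covers participants able to use that limb and, under the default complete-case ANOVA, only those able at all four sessions. That is a subset possibly shaped by post-allocation symptom state, and it does not meet the ITT definition given in the same section.

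The size and direction of any bias cannot be derived from the documents. The values in the working show only what particular assumptions would produce. The bias is zero if inability is fixed before allocation, or is unrelated to the arm or to the index; a loss of precision would remain. One secondary task is concerned, for one hand. Neither primary outcome is affected, so this is a low-cost improvement and not a threat to the trial's main conclusion.

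**What to change.** Analyse the affected-hand indices with the linear mixed model already named in Statistical analyses, using every session at which the affected-hand conditions were completed. Do not impute the missed sessions, and do not remove a participant for inability at one session. This includes people unable at baseline who later complete the task; a rule excluding only those unable at RS1 or RS2 would still miss them. Describe the result as conditional on ability to use the limb, not as ITT, and give the number unable by arm and session beside it.

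The cost is a reworded sentence and one mixed model per affected-hand index, with no new data. The downside is the assumption that inability is explained by the sessions that were observed, so the counts by arm must be read with the estimate. A participant with no completed affected-hand session still contributes only to the unaffected-hand analysis.

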
**Table 1 Tab1:**
[figure not shown]
Schedule of enrolment, interventions, and assessments for the participants with CRPS

*RS* Research Session, *LTFU* Long Term Follow-Up (postal questionnaires only), *PA* Prism Adaptations

*Primary endpoint of the study

**Secondary endpoint of the study

***Self-reported average levels of pain, range of movement and symptoms interference with daily life in the last 24 h, rated daily on 0–10 Numeric Rating Scales

Deviations from the schedule of consecutive Research Sessions and Follow-Ups will be accepted within the following time windows: up to 2-weeks deferral of RS2 and RS4, up to 1-week deferral of RS3, up to 3-weeks deferral of LTFU1 and LTFU2. If the times that the participant can attend RS2 and RS3 are planned to be longer than 14 days apart, the participant would commence the treatment 2 weeks before RS3. If the participant already started the treatment and has to postpone RS3, they would continue the treatment until RS3.

Twenty-one healthy control participants are being recruited for a single research session to obtain normative data. They undergo testing only once and do not receive any treatment.

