### Treatment

Participants in the PA treatment group are provided with welding goggles fitted with 35-diopter (∆) Fresnel lenses that induce a visual shift of approximately 19° away from the CRPS-affected side. The optical displacement is of a similar magnitude as in previous CRPS studies that reported significant reductions in pain [22–24]. In contrast, no pain reduction was observed when a CRPS patient underwent 2 weeks of PA using lenses that shifted the visual image only by 5° [24]. Furthermore, prisms strength of 10°-15° was found to be sufficient to induce lasting amelioration of hemispatial neglect after brain injury [14, 17, 18, 36, 37], whereas weaker prisms did not improve neglect [38]. During each treatment session, the participant is seated in front of a vertical surface, such as a wall, upon which an A4 laminated page in landscape orientation is positioned. The page displays two visual targets (red circles 2 cm in diameter), in each top corner. The page is mounted approximately at eye-level, hence targets are located 12.5 cm (approximately 10°) to the left and to the right of the participant’s body midline. The distance between their torso and the wall is established individually, such that the participant can touch the targets with an almost fully extended arm (approximately 60 cm). Participants put on the goggles and use their CRPS-affected arm to perform a total of 50 pointing movements (a number sufficient to induce sensory-motor adaptation [15]), alternating between the two targets (25 per side) and returning the pointing hand to their chest between each movement. The participants are instructed and trained to move as quickly as possible, and the goggles occlude the vision of the participant’s arm for approximately the first half of the movement. Both of these steps limit on-line correction of movement trajectory (strategic component of PA) and reinforce adaptive realignment, which is thought to maximise the effects of PA [12, 39, 40]. One treatment session takes approximately 5 min. The participant performs the treatment once under the guidance of an experimenter, and then twice daily for 2 weeks in a self-guided manner in their own home (giving a total of 29 treatment sessions). The intensity and duration of the treatment regime have been established based on previous studies evaluating the effects of PA on attention in hemispatial neglect following stroke, and on pain in CRPS. In particular, previous studies suggest that repeated sessions of PA are required to obtain a significant reduction in CRPS symptoms [22, 24] and that intense treatment (2 sessions a day for 4 days or more) produces symptom reduction that is sustained for at least 2 weeks post-treatment [22, 23].

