
Participants in the sham treatment group carry out the same procedure as the PA treatment group, except they are provided with goggles fitted with neutral lenses that do not induce optical deviation of the visual field. This is a standard control treatment for PA [17, 41]. Both prismatic and neutral lenses distort the acuity and clarity of vision, and both sets of goggles occlude the first part of the reaching movement. This factor ensures similarity of the two treatment arms in all aspects of the treatment aside from the sensory-motor adaptation.

To improve their adherence to the treatment protocol the participants receive in-person training, in which they complete the first treatment session guided by [name] or [name], who ensure participants’ competence in performing the exercise according to the protocol. Furthermore, participants are provided with written instructions and a video tutorial. The researcher who trained them in the treatment is also available to address any questions or concerns about the procedure by phone or email. In order to monitor participants’ compliance and adherence, they keep a daily logbook throughout the treatment period, in which they record the time and duration of each treatment session. We will report the adherence to treatment as a percentage of participants in each treatment group who did not miss more than 6 treatment sessions. The extent of exposure in each group will be reported as average number of logged treatment sessions. Protocol deviations are defined as missed or additional treatment sessions, and sessions for which logbook entries suggest that anything other than the trained procedure has been used. We will report the total number of treatment sessions per group in which deviations other than missed or extra sessions are suspected. We will also compare the average number of logged treatment sessions between the two groups, and if significantly different, the number of logged treatment sessions will be used as a covariate in the analyses of the primary outcomes.

The participants are instructed to continue their standard pharmaceutical, physical, and/or other treatments during the trial, and are encouraged not to make any significant alterations to these treatments (e.g., major changes in medication, commencing new physiotherapy programmes). Medications and other treatments are noted during every research session to monitor any changes.

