#### Primary outcomes

A change between RS2 (immediately before the commencement of treatment) and RS3 (immediately after the end of the treatment period) in current self-reported pain intensity and CRPS severity score [35, 52] are the primary outcomes. People with CRPS consider pain relief to be the highest priority for recovery [59], and pain intensity is the most common primary outcome in chronic pain trials [60]. Current pain intensity is measured using item 6 of the Brief Pain Inventory (BPI; short form) [42], which is a Numerical Rating Scale (NRS) ranging from 0 – “no pain” to 10 – “pain as bad as you can imagine”. The BPI has high reliability [42]. In addition to pain, CRPS involves a range of other debilitating symptoms, some of which were also affected by PA in previous studies [22, 24]. Therefore, we included a comprehensive measure of symptoms severity as the second primary outcome. The CRPS severity score assessment protocol follows the 16-points scoring system published by Harden and colleagues [35]. This continuous index of CRPS symptom severity has good discrimination abilities, concurrent validity and adequate sensitivity to change [35, 52], and has been recommended as one of the core outcome measures for CRPS clinical studies [61].

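### The supportive per-protocol rule ignores how sessions were performed and requires a visit after the primary endpoint, so it does not select the population it names

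*Protocol article*

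**What the plan says.** All references are to the Protocol article.

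- **Aim.** Treatment outcome analyses describes the per-protocol comparison as one between participants "who were able to perform it according to the trained protocol" and sham participants who did likewise.
- **Entry rule.** The same section then says "The PP population will be the subset of the ITT population who provided complete outcome data for RS1-RS4", explained as having "attended all in-person research sessions and completed the primary outcome measures) and missed no more than 6 treatment sessions". There is no other condition.
- **Deviations.** The Treatment section defines protocol deviations as missed sessions, additional sessions, and "sessions for which logbook entries suggest that anything other than the trained procedure has been used". The last kind is to be reported only as a total per group.
- **Endpoint.** Primary outcomes defines the outcome as "A change between RS2 (immediately before the commencement of treatment) and RS3" for both pain and CRPS severity score. The Design section names RS3 as the primary endpoint, and the RQ1 analysis section says that RS2 to RS3 is the change of main interest.
- **Session numbers.** The Treatment section describes one guided session and then two a day for two weeks, "giving a total of 29 treatment sessions". The time-window text with Table 1 allows RS3 to be deferred by up to a week and says of participants already on treatment that "they would continue the treatment until RS3".

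**The concern.** A per-protocol set is useful only if its members are the people described by the question it is meant to answer. Here the stated question concerns treatment performed as trained, but nothing in the entry rule looks at performance. The protocol itself holds that performance matters: the Treatment section says that fast movement and hiding the first part of the reach are what promote adaptive realignment. Sessions done another way may produce less adaptation and so blur the contrast between arms that this analysis is meant to isolate.

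The RS4 requirement raises a different problem. It makes membership for a contrast that ends at RS3 depend on something that happens afterwards. If staying until RS4 is related to how a participant fared, the per-protocol RS2-RS3 contrast is estimated in a group selected partly on outcome.

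**Working it through.** No effect size can be calculated, because the documents give no rate of flagged sessions or of missed RS4 visits. The check sets the rule against its aim.

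**Session count.** 1 guided + 2 × 14 = 29, which agrees with the plan. At most 6 missed means at least 29 − 6 = 23 logged, and 23/29 = 79.3%.

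**Rule against aim**, for four kinds of participant and the RS2-RS3 contrast:

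| Participant | Rule as written | Performed as trained, endpoint complete? |
|---|---|---|
| 29 logged, none flagged, RS1-RS4 complete | in | yes |
| 22 logged (7 missed), RS1-RS4 complete | out | no |
| 29 logged, 7 flagged for procedure, RS1-RS4 complete | in | no, if a flagged session counts like a missed one |
| 29 logged, none flagged, RS1-RS3 complete, RS4 absent | out | yes |

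The third and fourth rows are the two failures. In the third, the rule sets no ceiling: any number of the 28 self-guided sessions (29 − 1) could be flagged and the participant would still qualify.

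**Can RS4 absence depend on outcome?** Yes, by the protocol's own provisions. The Blinding section says that a participant who is unblinded because worsening symptoms concern them is withdrawn and gives no further data. If that happens between RS3 and RS4, someone who has worsened leaves the per-protocol set with the primary endpoint already recorded. The planned comparison of withdrawers with those who stay uses RS1 scores, so it can show baseline differences but not selection on response to treatment.

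**Does RS4 absence cost sample size?** The sample-size section's 21 per group reproduces with a two-sided normal approximation: 2 × (1.960 + 1.282)² × 1.98² / 2² = 20.6, rounded up to 21. That section and the recruitment and retention section define those 21 as complete RS1-RS4 datasets. Up to 52 people are enrolled, and anyone withdrawing before RS4 is replaced. A participant lacking RS4 is therefore additional to the 21, unless recruitment closes before the target is met.

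**Base of the limit of 6.** A one-week deferral of RS3 at two sessions a day adds 2 × 7 = 14, so 29 + 14 = 43 sessions are possible. Measured against 29, a participant logging 36 has 36 − 29 = 7 additional sessions and is in. Measured against 43, the same participant has 43 − 36 = 7 missed and is out. The text does not say which base applies, nor whether sessions continued under the deferral text are among the additional ones classed as deviations.

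**The case against.** Five points can be made for the plan.

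1. *The analysis is only supportive.* Intention to treat is primary. Participants without RS4 stay in it with their observed RS3 values. This stands and limits the weight of the point.
2. *RS4 completeness suits the repeated-measures model.* The CRPS severity ANOVA runs over RS1-RS4 and needs complete cells. That is a fair reason for that model, but it is not applied consistently: the pain ANOVA also uses LTFU1 and LTFU2, which membership does not require. The RS2-RS3 contrast itself needs only two sessions.
3. *Finer adjudication belongs in an analysis plan.* Often so. Here, though, the protocol states a complete rule beside its purpose, and the rule followed as written misses that purpose.
4. *Procedural deviations can only be suspected.* Adherence is self-reported, as the Discussion admits, and logbooks record mainly the time and duration of sessions. This stands as a limit on what any flag can detect. But the protocol already plans to identify and count these sessions, so using them adds no new judgement.
5. *Grossly wrong performance is unlikely.* A reader might picture someone doing all 29 sessions wrongly and still qualifying. The documents do not support that picture: the first session is guided by a researcher who ensures competence, and written instructions, a video and telephone or email support follow. The realistic case is a participant with some flagged self-guided sessions.

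Two other strong readings also fail. One is that each participant without RS4 costs 1/21, or about 5%, of an arm. Replacement to full RS1-RS4 datasets answers that. The other is that 43 sessions become due when RS3 is postponed, so that 36 logged means 7 missed. That is only one reading of an ambiguous text; counting from 29 is at least as natural.

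**Conclusion.** The point holds in limited form. The per-protocol rule does not match the population it names: flagged procedural deviations never affect membership, and an adherent participant with a complete primary endpoint can be excluded for missing a later visit. The second fault concerns selection, not sample size.

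The size is unknown. The selection argument assumes that some RS4 absences are related to outcome, which the Blinding section makes possible but does not quantify. The dilution argument assumes that flagged sessions adapt less well, which fits the protocol's own account. A reader might infer that the per-protocol analysis cannot answer its question at all, or that the trial's main conclusion is at risk. Neither follows: if few sessions are flagged and few RS4 visits missed, the set will be nearly right, and the primary intention-to-treat result does not depend on it.

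The unclear base for the limit of 6 is a separate ambiguity to be reconciled, not a demonstrated error.

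**What to change.** For the per-protocol RS2-RS3 contrast:

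- require RS2 and RS3 primary outcomes, and require RS4 only for contrasts that use it;
- when applying the existing limit of 6, treat logged sessions flagged for suspected procedural deviation as missed;
- have the flagging done by someone blind to allocation and outcome, and finished before allocations are released after the last RS4.

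Separately, reconcile the deferral text with Table 1, the Treatment section and the per-protocol definition. State how sessions done while RS3 is postponed are classified for analysis, and what total the limit of 6 refers to. This concerns counting only and takes no position on the treatment schedule.

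The cost is small: the logbooks and the flags are already planned. The per-protocol set may differ in size between RS3 and RS4 contrasts, so the RS2-RS3 contrast would be run on its own set as well as within the RS1-RS4 ANOVA, and both set sizes reported.
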